**Compliance Statement**

The protocol was approved by the Western Institutional Review Board (WIRB: Olympia, WA USA) following FDA and ICH guidelines. Written and informed consent was obtained from all subjects prior to enrollment.

**Study Endpoints**

*Efficacy Endpoints*

- Clinical grading at baseline, week 4, and week 8:
  - Face: Forehead wrinkles, cheek wrinkles, lip area wrinkles, global facial wrinkles, facial sagging, glabella lines, texture
  - Neck: Overall appearance, sagging, neck folds, texture
- Digital imaging procedures: Vectra 3D Imaging System, Canfield
- Subject completed self-assessment questionnaires (week 4 and week 8).

*Safety/Tolerability Endpoints*

- Clinical grading of objective irritation parameters and subject reporting of subjective assessment parameters at baseline, week 4, and week 8.
- Monitoring of adverse events throughout the course of the study.

Overview

| **Study Title** | Evaluating the efficacy of a prototype massage applicator using a prototype cream and manual application of a prototype cream on a population with signs associated with aging skin |
| --- | --- |
| **Sample Size** | 45 enrolled to complete 42 |
| **Study Design** | - 2 arms:   - tagged prototype massage applicator using a sonic handle and prototype cream   - Manual application of prototype cream - Subjects randomized to a treatment application method (prototype massage applicator + prototype cream, manual application of prototype cream) - Home use: two times per day; 7 days per week   - Prototype massage applicator using prototype cream for 2 minutes and 15 seconds (30 seconds forehead, 1 minute mouth and cheek area, and 45seconds jawline and neck)   - Manual application of facial cream (using their normal technique for applying facial creams) - Duration: 8 weeks - Study visits: Baseline, 4 and 8 weeks - Clinical assessments: Baseline, 4 and 8 weeks - Self-assessment questionnaires: 4 and 8 weeks   A sunscreen (SPF 30) will be given to subjects at the baseline visit for daily use (mornings only) and to be reapplied during the day as needed for the duration of the study |
| **Number of Arms** | 2 arms:   - Prototype massage applicator using a sonic handle and prototype cream - Manual application of prototype cream |
| **Test Sites** | - Face - Neck |
| **Key entrance criteria** | - Available for 3 study visits - Between the ages of 65-75 years - Have not participated in a study evaluating Anti-aging applicators/devices - Fitzpatrick skin types I, II, III - Non-smokers - Fine lines/wrinkles: global facial wrinkles ( ≥ 4 on a 10 pt. scale) - Sagging facial skin ( ≥4 on a 10 pt. scale) |
| **Parameters** | - Photographs at baseline, 4, & 8 weeks:   - Vectra 3D Imaging System - Expert/Esthetician clinical grading (face/neck):   - Face: Forehead wrinkles, cheek wrinkles, lip area wrinkles, global facial wrinkles, facial sagging, glabella lines, texture   - Neck: Overall appearance, sagging, neck folds, texture - Tolerance (0 – 3 point assessment scale):   - Objective tolerance: erythema, edema, dryness and peeling   - Subjective tolerance: burning, stinging, itching and tingling - Self-assessment questionnaires (4 & 8 week) |
| **Number of Visits/Study Duration** | - 4 visits/8 weeks |
| **Supplies needed** | - 23: handle - 23: Anti-aging massage applicator (RFID tagged) - 115: 2 oz jars Prototype cream   - 3 jars per subject for the device arm of the study   - 2 jars per subject for the manual arm of the study - 100: plastic spatulas - 45: SPF 30 sunscreen (4.2 oz tubes) - Cameras: Vectra - 45: Travel bags |
| **Visit Summary** | *Baseline (Visit 1):*   - 15 minute acclimation period - Study & photograph consent forms signed - Medical History reviewed - Assign study number to the subject - The examiner blinded to the application method will conduct the following:   - Tolerance (0 – 3 point scale):     - Objective tolerance: erythema, edema, dryness and peeling     - Subjective tolerance: burning, stinging, itching and tingling   - Clinical grading assessments on the face and neck (0-9 point scale):     - Face:       - forehead wrinkles       - cheek wrinkles       - lip area wrinkles       - global facial wrinkles       - facial sagging       - glabella lines       - texture     - Neck:       - overall appearance       - sagging       - neck folds       - texture - Photos prior to product use: Vectra - Study personnel not blinded to the application method will randomize the subject to a treatment group - Study personnel not blinded to the application method will train the subject on product use:   - Have subjects examine their face and neck in a mirror prior to product use with study personnel pointing out areas to follow for the duration of the study; fine lines and wrinkles, sagging, texture, neck folds, glabella lines, overall appearance, etc.   - For subjects randomized to the *manual application groups*:     - No instructions on how to or how long or how much facial cream to apply the face and neck will be given. Subjects will be instructed to apply the study cream using the amount of cream and technique of application they normally use at home when applying a facial cream     - Subject applies the study cream to the face and neck using the amount of cream and technique they normally use at home to apply facial creams     - Subjects will be instructed to apply the study cream twice per day (morning and bedtime)   - For subjects randomized to the prototype device group:     - Subjects will be trained on how to use prototype device     - The study personnel will explain and demonstrated to the subjects how much cream to use with the anti-aging applicator and how to apply the cream to the treatment zones (refer to Volunteer Instructions)     - Subjects applies the prototype study cream to each treatment zone (forehead, cheeks/mouth and neck/jawline) for a total of 2 minutes and 15 seconds using the prototype device /prototype cream for the following times per treatment zone:       - Zone 1: forehead - 30 seconds       - Zone 2: cheeks and mouth area - 1 minute       - Zone 3: neck and jawline – 45 seconds     - Discontinue all current serum, moisturizer, and/or any other skincare products     - Subjects will be instructed to use the study products twice per day (morning and bedtime) - Remind subjects to bring all study products to next study visit - Instruct subjects to discontinue using their current serum, moisturizer, and/or any other skin care products and replace with study products - A sunscreen SPF 30 will be given to the subjects with instructions to apply the sunscreen every morning and to reapply throughout the day as needed   *Visit 2 & 3 [Visit 2[4 weeks (28 days ±2 days) post baseline], Visit 3 [8 weeks (56 days ±2 days) post baseline]*   - 15 minute acclimation period - Review medical history and discuss product use - Document adverse events and protocol deviation as indicated - Confirm subject has applied the study products per application method at least 2 hours prior to the study visit. - Confirm subject has no makeup, skin care products (eye products/eye makeup permitted) including sunscreen on the face and neck the morning of the study visit (besides study cream) - The examiner blinded to the application method will conduct the following:   - Tolerance (0 – 3 point scale):     - Objective tolerance: erythema, edema, dryness and peeling     - Subjective tolerance: burning, stinging, itching and tingling   - Clinical grading assessments on the face and neck (0-9 point scale):     - Face:       - forehead wrinkles       - cheek wrinkles       - lip area wrinkles       - overall facial wrinkles       - facial sagging       - glabella lines       - texture     - Neck:       - overall appearance       - sagging       - neck folds       - texture - Photos prior to product use: Vectra - Subject completes a self-assessment questionnaire - Additional product dispensed if needed (Visit 2 only)   Study products collected and subject compensated for participation (Visit 3 only) |
|  |  |
|  |  |

# **Volunteer Selection**

A. Population:

45 volunteers will be enrolled in this 8 week study to complete 42.

B. Enrollment Criteria:

*Inclusion criteria:*

Volunteers meeting the following criteria will be enrolled:

- Between the ages of 65-75 years;
- Available for 3 study visits;
- Have not participated in a study evaluating anti-aging applicators/devices;
- Fitzpatrick skin types I, II, III, IV
- Fine lines/wrinkles: global facial wrinkles ( ≥ 4 on a 10 pt. scale);
- Sagging facial skin ( ≥ 4 on a 10 pt. scale);
- Individuals who are non-smokers;
- Individuals that are willing to provide written informed consent and are able to read, speak, write, and understand English;
- Individuals willing not to wear makeup or use skin care products other than the study products the day of the study visits;
- Individuals willing to discontinue using current skincare products and only use study products for the study duration
- Individuals willing to refrain from sun tanning / sun bathing for the study duration.

*Exclusion criteria:*

Volunteers will be excluded from the study if they meet any of the criteria listed below:

- Present or disclose any medically diagnosed chronic skin problems on their face (e.g., psoriasis, eczema, seborrheic dermatitis, or chronic cystic acne, etc.)
- Diagnosed with known allergies to facial skin care products
- Have undergone dermatological skin rejuvenation procedures such as light-therapies (IPL, lasers, radiofrequency and other lights treatments ) or such as collagen or other facial tissue augmentation, fillers, or retail microdermabrasion on the face within the last 1 year preceding the baseline visit and intended to receive them during the study period
- Have undergone Botox treatment on the face within the last 6 months preceding the baseline visit and intend to receive them during the study period
- Have a history of immunosuppression/immune deficiency disorders (including HIV infection or AIDS) or currently using immunosuppressive medication (e.g., azathioprine, belimumab, cyclophosphamide, Enbrel, Imuran, Humira, mycohenolate mofetil, methotrexate, prednisone, Remicade, Stelara)
- Have uncontrolled disease such as diabetes, hypertension, hyperthyroidism, or hypothyroidism. Individuals having multiple health conditions may be excluded from participation even if the conditions are controlled by diet, medication, etc.
- Have planned surgeries or invasive procedures during the course of the study.
- Have hypersensitive skin to chemical agents.
- Excessively tanned face before the baseline visit and who intend to excessively be exposed to sun or artificial U. V. during the study period
- Have hypersensitive skin to chemical agents
- Have sunburned skin
- Are an employee of Clarisonic

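### The facial-procedure and Botox exclusions, and to a lesser degree the tanning exclusion, join past exposure and future intent with *and*, so recent exposure alone does not exclude a volunteer

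*Protocol*

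**What the plan says.** In the Protocol, Volunteer Selection, B. Enrollment Criteria, the exclusion list opens with this rule: "Volunteers will be excluded from the study if they meet any of the criteria listed below". One bullet is therefore enough to exclude, provided that bullet is met.

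Three bullets contain two conditions each:

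- **Rejuvenation procedures** (light-based treatments, fillers and other tissue augmentation, retail microdermabrasion, on the face): "within the last 1 year preceding the baseline visit and intended to receive them during the study period".
- **Botox:** "Have undergone Botox treatment on the face within the last 6 months preceding the baseline visit and intend to receive them during the study period".
- **Tanning:** "Excessively tanned face before the baseline visit and who intend to excessively be exposed to sun or artificial U. V. during the study period".

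Two other criteria in the same section touch the future half. One exclusion reads "Have planned surgeries or invasive procedures during the course of the study" and does not define the term invasive. One inclusion item reads "Individuals willing to refrain from sun tanning / sun bathing for the study duration". A separate exclusion covers sunburned skin.

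**The concern.** A look-back window has little purpose unless recent exposure is disqualifying in itself. Here the 1-year and 6-month windows count only for volunteers who also plan more treatment during the study.

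The list does not use *and* as a loose substitute for *or* throughout. In the immunosuppression bullet, a history of the condition and current use of the medication are joined by *or*, so that either one excludes. A reader who takes the list at its word has reason to read the three bullets differently from that one.

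These exposures bear on what is graded: forehead, cheek, lip and global wrinkles, glabella lines, facial sagging and texture. A treatment that fades between baseline and week 8, or is added in that time, can change a grade without any contribution from the cream or the applicator. The trial is small (45 enrolled to complete 42), and its threshold for clinical significance is half a point. A few such subjects could therefore matter, and eligibility cannot be corrected after enrolment.

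**Working it through.** The protocol has no figure of its own to reproduce. The check is a logical reading, followed by an illustration of size.

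**Step 1. Each bullet alone.**

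| Recent exposure | Intends exposure during study | Excluded with *and* (as written) | Excluded with *or* |
|---|---|---|---|
| yes | yes | yes | yes |
| yes | no | no | yes |
| no | yes | no | yes |
| no | no | no | no |

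Of the three combinations that involve an exposure, each bullet as written removes one.

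**Step 2. The other criteria.**

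| Volunteer | Other criterion that applies | Result |
|---|---|---|
| Recent facial procedure or Botox, none planned | None | Eligible |
| Already excessively tanned, no exposure planned | Sunburn exclusion, only if burned | Otherwise eligible |
| Botox or filler planned, none before | Planned surgeries or invasive procedures | Possibly excluded; depends on the meaning of invasive |
| IPL, laser, radiofrequency or microdermabrasion planned, none before | Same bullet | Not clearly excluded |
| Sun exposure planned, not tanned | Inclusion item on sun tanning and sun bathing | Largely excluded; artificial UV is not named |

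The key entrance criteria in the Overview do not mention these exposures. The inclusion items on skin care, and the Volunteer Instructions, concern products and routines and name no procedures. The first row is therefore fully open, the second is open unless the skin is burned, and the other three are open in part.

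**Step 3. Illustrative size.** From the protocol: 42 completers, so 42/2 = 21 per arm if split evenly; half-point clinical threshold; 45 enrolled, taken here as 23 and 22. Assumed, because the protocol gives none of them: SD of change 0.5 to 1.0 point, two affected subjects per arm, each drifting by d = 1 to 2 points.

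- *Variance.* With f = 2/21 = 0.095, the ratio is 1 + d²f(1−f)/SD², where f(1−f) = 0.0862.
  - SD 1.0, d = 1: 1 + 0.0862/1 = 1.09.
  - SD 0.75, d = 2: 1 + 4 × 0.0862/0.5625 = 1.61, so 21 subjects carry the information of 21/1.61 = 13.0.
  - SD 0.5, d = 2: 1 + 4 × 0.0862/0.25 = 2.38.
- *Mean shift if two such subjects fall in one arm and none in the other.* 2d/21 = 0.095 to 0.190 point, which is 19% to 38% of the half-point threshold. At SD 0.75 the standard error of the arm difference without such subjects is 0.75 × √(2/21) = 0.23, so the shift is 0.4 to 0.8 of a standard error.
- *Chance of an uneven split.* If four such subjects are enrolled, P(2:2) = C(23,2) × C(22,2)/C(45,4) = 253 × 231/148,995 = 0.39. The arms then differ by at least two of them with probability 0.61.
- *Power under the planned tests.* The Statistical Analysis section switches from the t-test to Mann-Whitney when Shapiro-Wilk gives p≤0.01. A simulation with a true difference of 0.5 point, 21 per arm and two affected subjects in each arm, applying Shapiro-Wilk to each arm, gave:

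| SD | Drift | Power, no affected subjects | Power, planned procedure | Power, t-test only |
|---|---|---|---|---|
| 0.5 | 2 | 0.89 | 0.71 | 0.55 |
| 0.75 | 1 | 0.56 | 0.50 | 0.50 |
| 0.75 | 2 | 0.56 | 0.36 | 0.33 |

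**The case against.** **Staff will know what was meant.** The windows make the intention fairly plain, and staff may well apply each half separately. The online qualification questionnaire and the inclusion/exclusion checklist, which put the criteria into practice, are not in the document. So it is not shown that any such volunteer would be enrolled, and that part of the objection stands. It does not rescue the text: a form copied from it would admit these volunteers, and staff who read it differently from one another would apply eligibility inconsistently.

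**Planned exposure is covered elsewhere.** A reader might infer that anyone who plans a course of treatment but has had none is admitted. The protocol does not support that. The planned-procedures exclusion may catch injections, and the sun-tanning inclusion item covers most tanning intent. Only the remainder set out in the second table of the working is open.

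**The effect is bias.** A reader might infer this too. Subjects are randomized, so an uneven split is chance imbalance, not systematic bias. The 0.61 is simply the chance that four subjects do not divide two and two.

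**The figures reflect their assumptions.** This stands. SD, drift and the number of affected subjects are all assumed. Two per arm is about 10% of the sample, and a drift of 1 to 2 points is two to four times the clinical threshold. The switch to a rank test recovers part of the loss when outliers are extreme, so the 2.38 variance ratio overstates the damage in that case. The procedure and Botox bullets concern treatment on the face, while four of the eleven grades are neck grades. No mechanism specific to tanning is established for the graded outcomes.

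**Conclusion.** The rule is wrong as written. Taken literally, the procedure and Botox bullets admit volunteers with recent exposure and no further plans, and no other criterion closes that gap. The tanning bullet has the same fault to a lesser degree. This conclusion rests on the wording alone.

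The consequence is added noise in the facial grades and possible chance imbalance between small arms. Its size cannot be derived from the protocol. The illustrations run from slight (variance up 9%, or power from 0.56 to about 0.50) to substantial (power from 0.56 to 0.36), depending entirely on the assumed inputs.

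Severity is moderate. A reader might infer that the trial cannot proceed without the change, but no sample size, significance level or choice of test depends on this wording, and the protocol does not show how many such volunteers would come forward.

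**What to change.** Make each half of the three bullets exclude on its own, either by replacing *and* with *or* or by splitting each bullet into two:

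- facial rejuvenation procedure within the existing 1-year window, or intention to have one during the study;
- facial Botox within the existing 6-month window, or intention to have it during the study;
- excessively tanned face at baseline, or intention of excessive sun or artificial UV exposure during the study.

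Reconcile these with the planned-procedures exclusion, stating what counts as invasive, and with the sun-tanning inclusion item, stating whether it covers artificial UV. Carry the same wording into the online screening form and the inclusion/exclusion checklist before screening starts.

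The cost is one word in three bullets, the two clarifications and the matching form edits. The downside is a slightly smaller recruitment pool.

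### Three exclusions join a past condition to a future intention with *and*, so recently treated or already tanned volunteers remain eligible; the Fitzpatrick range also differs between two sections

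*Protocol*

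**What the plan says.** The exclusion list in the Protocol's Volunteer Selection section opens with the rule "Volunteers will be excluded from the study if they meet any of the criteria listed below". Each bullet is therefore a separate test, and a volunteer is excluded only by meeting at least one bullet in full.

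Three bullets have two halves joined by *and*:

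- **Rejuvenation procedures.** After naming light therapies, lasers, radiofrequency, collagen and fillers, the bullet ends "microdermabrasion on the face within the last 1 year preceding the baseline visit and intended to receive them during the study period".
- **Botox.** "Botox treatment on the face within the last 6 months preceding the baseline visit and intend to receive them during the study period".
- **Tanning.** "Excessively tanned face before the baseline visit and who intend to excessively be exposed to sun or artificial U. V. during the study period".

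Two other criteria touch the same ground, but only for the future. One exclusion removes volunteers with surgery or invasive procedures planned during the study. One inclusion criterion requires willingness to avoid sun tanning and sun bathing for its duration.

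On skin type, the key entrance criteria in the Overview table list "Fitzpatrick skin types I, II, III", while the inclusion criteria in Volunteer Selection list "Fitzpatrick skin types I, II, III, IV".

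**The concern.** A look-back window is meant to keep out volunteers whose skin still carries the effect of an earlier procedure. Tied by *and* to an intention to repeat, it does not do that. A volunteer treated shortly before baseline passes, provided no further treatment is planned.

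Forehead wrinkles, glabella lines and sagging are graded endpoints, and the Statistical Analysis section tests each arm's scores against its own baseline at weeks 4 and 8. On a scale where higher is worse, an effect that fades over the 8 weeks raises the later scores and can hide an improvement. A procedure received during the study would act the other way and be credited to the product.

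The Fitzpatrick discrepancy is a separate matter of consistency. A type IV volunteer is eligible under one section and ineligible under the other, so the target population, and what counts as an eligibility deviation, depend on which section the site uses.

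**Working it through.** The Protocol states no figure to reproduce. The check is one of logic, followed by a comparison with the other criteria.

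**Step 1: what each bullet excludes.** Let A be the past condition (procedure within 1 year, Botox within 6 months, or excessive tan before baseline) and B the future intention. The bullet excludes those with A and B together.

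| Volunteer | Excluded by the bullet? | Caught by another criterion? | Result as written |
| --- | --- | --- | --- |
| A and B | Yes | – | Excluded |
| A only, recent procedure or Botox | No | No | Eligible |
| A only, tanned at baseline | No | No; the sunburn exclusion concerns a different condition | Eligible |
| B only, planned procedure | No | Partly: the planned-invasive-procedure exclusion may catch injections; light treatments or microdermabrasion may escape | Unclear |
| B only, planned sun exposure | No | Largely: the inclusion criterion on avoiding tanning | Mostly excluded |

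The gap is clear in the two A-only rows. Anyone a bullet excludes must also hold the intention, so the 6-month and 1-year windows exclude nobody by themselves.

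**Step 2: do the severity thresholds close the gap?** Entry requires at least 4 on global facial wrinkles and on facial sagging. This may keep out some volunteers whose treatment is still fully effective. It sets no minimum for forehead wrinkles or glabella lines, so a volunteer can meet both thresholds with those areas recently treated.

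**Step 3: which analyses are exposed.** Grading at baseline comes before randomization, and the examiner is blinded to the application method. Prior treatment is therefore unrelated to arm except by chance. The comparison between arms gains variance and possible chance imbalance, but no systematic bias. The paired tests against baseline have no such protection, because any drift is part of the change being tested.

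**Step 4: size.** The Protocol gives no rate of prior procedures, no drift and no SD, so the effect cannot be computed. What can be shown is how it scales. Assume 42 completers split equally, 42/2 = 21 per arm, with k affected subjects in an arm each drifting d points:

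- Shift in that arm's mean change = (k/21) × d. With k = 2 assumed: d = 1 gives 2/21 × 1 = 0.10; d = 2 gives 0.19; d = 3 gives 0.29.
- Shift in the difference between arms = (k₁ − k₂)/21 × d. With two affected in one arm and none in the other it is again 0.10 to 0.29; with two in each arm it is 0.

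Both k and d are assumptions. The only Protocol figure to set beside them is the half-point threshold for clinical significance.

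**Step 5: Fitzpatrick.** Overview: I, II, III. Inclusion criteria: I, II, III, IV. The lists differ by type IV, and nothing in the Protocol says which governs.

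**The case against.** The strongest reply is that the intent is obvious: any site would read these bullets as excluding on either condition. That may well be so, but nothing in the Protocol says it. The baseline procedures have staff verify an eligibility checklist, and a checklist taken from this text would carry the same connective.

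Several stronger readings are tempting and are not supported:

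- **A volunteer planning fillers mid-study is eligible.** A reader might infer this from the procedure bullet alone. The separate exclusion for planned invasive procedures can reasonably be read to cover injections, so the statement does not hold flatly.
- **Future tanning is uncontrolled.** The inclusion criterion largely covers it. What is left is the volunteer already tanned at baseline, and the Protocol shows no effect of tanning on graded wrinkles or sagging.
- **The treatment comparison is biased.** Randomization after baseline grading and a blinded examiner rule out systematic bias from prior procedures.
- **The arm mean moves by about 0.19 points.** That value needs an assumed number of affected subjects and an assumed drift. As a difference between arms, it also needs all of them in one arm.
- **The face-only exclusions are an error because the neck is a test site.** The neck carries 4 of the 11 graded efficacy parameters, and the skin-problem exclusion covers only "medically diagnosed chronic skin problems on their face". But the severity entry criteria are facial too, and no section says that neck procedures must be excluded. This is a choice of scope.

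These points narrow the concern to recent treatment, or an existing tan, without future intent. They do not remove it.

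**Conclusion.** The point holds in this limited form. As worded, volunteers with recent Botox, fillers or laser and no plan to repeat are eligible, as are those already excessively tanned who agree to refrain. This rests on the literal text, on the rule that any single bullet excludes, and on the absence of any other criterion covering past treatment or an existing tan.

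The exposed analysis is the within-arm change from baseline. The randomized comparison is affected only through variance and chance imbalance. The size cannot be determined from the Protocol; the 0.10 to 0.29 points above shows scaling under stated assumptions and is not an estimate.

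The Fitzpatrick mismatch is a plain contradiction between two sections. No effect on the results is claimed for it, and the Protocol gives no basis for preferring either range.

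**What to change.** In the rejuvenation-procedure and Botox bullets, change the connective before the intention clause from *and* to *or*, using *intend* in both. In the tanning bullet, change *and who intend* to *or who intend*. Carry the same wording into the eligibility checklist and the online screening questions.

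Separately, reconcile the Overview table and the inclusion criteria to a single Fitzpatrick range before screening begins.

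Optionally, state whether the skin-problem and procedure exclusions are meant to cover the neck as well as the face.

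The cost is a few words in the Protocol and the screening documents, and a few more screen failures. The design, visits and analysis do not change.
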